
## Methods

### Study setting

A total of 802 patients will be recruited from five centers: the main responsible unit, Xixi Hospital of Hangzhou, will recruit 162 cases, Beijing ShunYi Traditional Chinese Medicine Hospital will recruit 160 cases, the Sixth People’s Hospital of Shenyang will recruit 160 cases, Beijing DiTan Hospital Capital Medical University will recruit 160 cases, Chengdu University of Chinese Medicine Affiliated Hospital will recruit 160 cases. Figure 1 shows the flowchart of the trial.

**Fig. 1 Fig1:**
[figure not shown]
Flowchart of the randomized, placebo-controlled, double-blinded trial of YQSH for CHB. *CHB* chronic hepatitis B, *YQSH YinQiSanHuang*-antiviral decoction, *HBV* hepatitis B virus, *HBsAg* hepatitis B surface antigen, *HBeAg* hepatitis B e antigen, *ALT* alanine aminotransferase, *AST* aspartate aminotransferase, *GGT* gamma-glutamyl transferase, *ALP* alkaline phosphatase, *ALB* serum albumin, *TBIL* total bilirubin

### Eligibility criteria

#### Inclusion criteria

The inclusion criteria are as follows: (1) patients who have a history of hepatitis B infection or HBsAg positive for more than 6 months, and their current HBsAg and/or HBV DNA levels are still positive; (2) patients who meet the criteria for antiviral indications in the “Asian-Pacific consensus statement on the management of CHB: a 2008 update” [27]; patients taking entecavir dispersible tablets may also be included. (This study will enroll patients who have taken entecavir previously; conversely, patients who have taken immune stimulatory drugs or other antiviral drugs within 3 months will not be enrolled.); (3) patients between 18 to 65 years old; (4) patients showing syndromes of liver stagnation and spleen deficiency and dampness in TCM. For the TCM diagnostic criteria, we refer to “National Standards for TCM Clinical Diagnosis and Treatment in the People’s Republic of China” [28] and the “Medical Consensus of diagnosis and treatment of cirrhosis with integrated TCM and Western medicine” [29], published by the Digestive System Diseases Committee, Society of Integrated Traditional Chinese and Western Medicine.

#### Exclusion criteria

The exclusion criteria are as follows: (1) patients with cirrhosis; (2) patients with liver cancer; (3) patients in acute and chronic hepatitis with non-HBV infection, autoimmune hepatitis, primary biliary cirrhosis, primary sclerosis cholangitis, inherited metabolic liver disease, drug or toxic hepatitis, or alcoholic liver disease; (4) pregnant or lactating women or women planning to become pregnant during the study period; (5) patients who are allergic to the test drugs; (6) patients who have mental disorders and cannot cooperate with the study, or patients with epilepsy in unstable status; (7) patients with severe systemic disease related to the heart, brain, lung, kidney, or hematopoiesis; (8) patients with alcoholism or other unsuitable conditions for enrollment. Patients who are already using TCM will not be enrolled unless they have stopped using TCM for more than 3 months.

### Interventions

#### Description

All patients will have a screening test during the screening period in clinic if they meet the inclusion criteria. The screening evaluation includes the patient’s general status, disease-related symptoms and signs, and corresponding laboratory tests, including the following: urine pregnancy test (women of childbearing age), HBV DNA, liver function, FibroScan, liver B-mode ultrasound or magnetic resonance imaging (MRI)/computed tomography (CT), and other examinations. The test group (YQSH group) will receive YQSH formula granules 5 g (first brewed with 150–200 ml water) twice a day, combined with entecavir 0.5 mg once a day. The control group (placebo group) will receive YQSH placebo formula granules 5 g (first brewed with 150–200 ml water) twice a day, combined with entecavir 0.5 mg once a day. The entecavir was produced by ChiaTai TianQing Pharmaceuticals in Jiangsu, China (production batch number H20100019). The main components of YQSH, totaling 14 kinds of herbs, are shown in Table 1. The test drugs are made into Chinese medicine formula granules. Before taking YQSH, the mixed formula granules are boiled with 150–200 ml water for 3–5 min. The YQSH placebo is made of excipients, thinners, coloring agents, flavoring agents, and fried malt, and is similar to YQSH in shape, color, smell, and taste.

**Table 1 Tab1:** Main components of *YinQiSanHuang*-antiviral decoction

Chinese name	Latin name	English name	Pharmacological action	Main active ingredient	Original producing area	Medicinal part	Dosage (g)
*Huang Qi*	*Astragalus propinquus* Schischkin	Radix Astragali	Promotes liver cell growth, anti-liver fibrosis, antiviral, regulates immunity	Astragaloside (I,V, III), calycosin	Neimenggu, China	Rhizome	12
*Yin Chen*	*Artemisia capillaris* Thunb.	Virgate wormwood herb, capillary wormwood herb	Lowers blood lipids to treat fatty liver, reduces alcoholic liver damage, inhibits the replication of hepatitis B virus DNA	Capillin, capillene, capillanol, capillarisin, 6, 7-dimethylsculetin	Shanxi, China	Aboveground part of the plant	12
*Huang Qin*	*Scutellaria baicalensis* Georgi	Baical skullcap root	Anti-hepatocyte inflammation, anti-hepatocyte apoptosis, anti-hepatocyte mitochondrial lipid peroxidation, regulates immunity	Baicalein, neobaicalein, skullcap flavone II, baicalin, wogonin	Hebei, China	Rhizome	3
*Huang Lian*	*Coptis chinensis* Franch.	Coptis root	Anti-hepatocyte mitochondrial lipid peroxidation, inhibits hepatoma cell proliferation, prevents liver fibrosis	Berberine, coptisine, epiberberine, berberrubine, palmatine	Sichuan, China	Tuber root	3
*Huang Bai*	*Platycladus orientalis* (Linn.) Franco	Bark of Chinese corktree	Inhibits immune response, selectively inhibits HBAg, anti-inflammatory	Berberine, phellodendrine, magnoflorine, jatrorrhizine, palmatine	Sichuan, China	Dry bark	3
*E Zhu*	*Curcuma aeruginosa* Roxb. [*C. zedoaria* Rosc.]	Rhizome curcumae	Inhibits hepatoma cell proliferation, induces apoptosis of liver cancer cells, anti-liver fibrosis	Volatile oil (turmerone, borneol, curcumol), curcumene, curdione, turmeric	Guangxi, China	Tuber root	6
*Bie Jia*	*Trionyx sinensis* (Wiegmann)	Turtle shell	Anti-liver fibrosis, promotes immunity, anti-hepatocyte injury	Collagen, *Trionyx sinesis* polysaccharides, amino acids (aspartic acid, threonine, glutamic acid), calcium carbonate, calcium phosphate	Hubei, China	Carapace	3
*Jiao Shan Zha*	*Crataegus pinnatifida* Bunge var. major N.E. Br.	Hawthorn fruit	Lowers cholesterol, anti-bacterial, anti-hypertensive	Epicatechin, quercetin, hyperoside, chlorogenic acid, anthocyanin, ursolic acid	Shandong, China	Fruit	15
*Bai Shao*	*Paeonia lactiflora* Pall.	Radix paeoniae alba	Anti-hepatocyte injury, anti-liver fibrosis, anti-fatty liver	Paeoniflorin, oxy-paeoniflorin, benzoylpaeoniflorin, albiflorin, paeoniflorigenone	Anhui, China	Rhizome	12
*Ling Xiao Hua*	*Campsis grandiflora* (Thunb.) K. Schum.	Trumpet creeper flower	Anti-oxidation, inhibits thrombosis, anti-inflammatory	Apigenin, β-sitosterol	Jiangsu, China	Flower	6
*Bai Zhu*	A*tractylodes macrocephala* Koidz.	Largehead atractylodes rhizome	Inhibits liver cancer cell metastasis, promotes cellular immune function, inhibits the activating of metabolic enzymes	Volatile oil (humulene, β-elemol, α-curcumene, α-atractylone, 3β-acetoxyatractylone), sesquiterpene lactone compounds (atractylenolide, 8β-ethoxyatractylenolide-II), polyacetylene(14-acetyl-12-senecioyl-2E,8Z,10E-atracetylentriol)	Zhejiang, China	Tuber root	9
*Fu Ling*	*Poria cocos* (Schw.) Wolf.	Tuckahoe	Enhances cellular and humoral immunity, inhibits the DNA synthesis of tumor cells, inhibits hepatocyte necrosis, anti-tumor	Pachymic acid, tumulosic acid, pachymic acid methyl ester, pachy-man, pachymaran	Yunnan, China	Dry sclerotia	9
*Chai Hu*	*Bupleurum chinense* DC.	Red thorowax root	Anti-liver fibrosis, inhibits acute liver injury, inhibits proliferation of liver cancer cells, promotes apoptosis of liver cancer cells, anti-liver injury	Volatile oil (pentanoic acid, hexanoic acid, heptanoic acid, 2-heptenoic acid)	Hebei, China	Rhizome	6
*Bai Hua She She Cao*	*Hedyotis diffusa* Willd.	Spreading hedyotis herb	Enhances hepatocyte immunogenicity, anti-tumor, inhibits proliferation of liver cancer cells, promotes apoptosis of liver cancer cells	Asperuloside, asperulosidic acid, deacetylasperulosidicacid, geniposidic acid, scandoside	Guangxi, China	Whole plant	12

#### Modifications

If a patient shows abnormal liver function (such as ALT > 2*ULN) during the trial, this should prompt temporary or permanent cessation of treatment, and the investigator can add hepatoprotective drugs such as silibinin and/or other drugs according to the patient’s condition. At the same time, the researchers will record and follow up the situation of the patient closely. If the patient’s ALT returns to normal after liver protection treatment, with normal values for direct bilirubin and international normalized ratio (INR) at the same time, then he/she may have a chance to continue the trial; otherwise, the patient will stop the trial permanently for safety reasons. If the following conditions occur, subjects should discontinue the trial: (1) poor compliance, irregularly taking medicine, failure to revisit or revisit on time; (2) some combined diseases or complications, or deterioration during the trial; (3) subject self-withdrawal; (4) combining trial drug with other drugs, or not taking test drugs according to research regulations; (5) lost contact; (6) cannot provide complete information.

We also list the following specific stopping criteria. (1) Serious safety problems occur during the test; then the test should be stopped in a timely manner. (2) The drug is found to have no clinical value during the trial; then the trial should be stopped to avoid delaying the effective treatment of subjects. (3) It is found during the trial that there is a major error in the clinical trial protocol and it is difficult to evaluate the effect of the drug; or there is a well-designed protocol with important deviations in the implementation, and it is difficult to continue to evaluate the efficacy and safety of the drug. (4) The sponsor requests to stop the trial (for funding reasons, management reasons, etc.). (5) The State Food and Drug Administration of China orders the trial to be stopped for some reason. (6) The test is suspended due to *force majeure* reasons.

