### Outcomes

#### Primary outcome

The primary outcome is the annual incidence of cirrhosis (the examination methods include instantaneous liver elastic hardness test, abdominal B-mode ultrasound test, or abdominal MRI/CT imaging).

The primary outcome is evaluated before the treatment, at 52 weeks of treatment, and at the 52 ± 2 weeks follow-up visit.

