#### Data collection plan and data management

The investigator will prepare original documents for each subject who was randomized into the study, and the information will be recorded in the CRF. All research results (personal data, test documents, etc.) that appear in the original medical records will be completely confidential within the scope allowed by law. Subject names will not appear in the CRF; only the name initials and the random number will be shown. The content should be comprehensive and accurate so as to record all examination results and other relevant data. The research center shall keep these documents properly for 5 years after the end of the research. The researcher will authorize the relevant regulatory agency to directly access all research-related documents.

There are principles for handling loss to follow-up: (1) if the loss is due to adverse reactions, the data will be recorded in the adverse reaction statistics; (2) if the loss is due to ineffectiveness, the data will be included in the efficacy statistics; (3) for those patients who were effective during the treatment but could not complete the entire course, and those lost to follow-up, these data will be included in the efficacy statistics and should be analyzed intentionally.

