#### Analysis population and missing data

We will use three methods for statistical analysis of the data:
Full analysis set (FAS). According to the intention-to-treat (ITT) principle, all randomized subjects’ data will enter the FAS. For subjects who withdraw from the study early for various reasons, the missing data will be imputed using the method of last observation carried forward (LOCF).Per protocol set (PPS). The study’s PPS will consist of the indicator data for those who enter the study and complete treatment and follow-up, whose medication compliance is 80–120%, who took no combined medication that affected the effectiveness evaluation during the study period, and who have complete evaluation index data and no major test protocol violations.Safety set (SS). The SS includes those subjects who received at least one treatment after randomization.

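### Patients taken off the trial before week 52 for liver abnormality, deterioration or non-adherence are recorded as cirrhosis-free by LOCF

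*Protocol article*

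**What the plan says.** All references are to the protocol article.

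- **Modifications.** A patient with abnormal liver function stops treatment temporarily or permanently. If ALT, direct bilirubin and INR return to normal, the patient may resume; "otherwise, the patient will stop the trial permanently for safety reasons". The next sentence begins "If the following conditions occur, subjects should discontinue the trial" and gives six reasons. They include poor compliance, "some combined diseases or complications, or deterioration during the trial", and "combining trial drug with other drugs, or not taking test drugs according to research regulations", alongside self-withdrawal and lost contact.
- **Exclusion criteria.** Patients with cirrhosis are not enrolled.
- **Primary outcome.** "The primary outcome is evaluated before the treatment, at 52 weeks of treatment", and at the follow-up visit 52 ± 2 weeks later. The 26-week visits listed under Secondary outcomes do not include it.
- **Analysis population and missing data.** The full analysis set (FAS) holds all randomised patients under the intention-to-treat principle. For early withdrawals, "the missing data will be imputed using the method of last observation carried forward (LOCF".
- **Data collection plan and data management.** "if the loss is due to ineffectiveness, the data will be included in the efficacy statistics". Patients who responded but did not finish the course are kept in the same way, as are "those lost to follow-up, these data will be included in the efficacy statistics and should be analyzed intentionally". The Adherence section repeats the last part.
- **Additional analyses.** No sensitivity analysis is planned.

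**The concern.** Each rule is unremarkable alone; together they turn removal from the trial into a favourable primary outcome. Patients who leave because liver tests stay abnormal, or because their disease worsens, are plausibly closer to cirrhosis than the rest. The only scheduled cirrhosis result they have before week 52 is the baseline one, which eligibility makes negative, and LOCF carries it forward.

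Two consequences follow. If removal is similar in both arms, events are lost and the absolute difference shrinks. If removal differs by arm, the comparison is biased towards the arm that loses more patients, or more high-risk patients. Unequal removal is not far-fetched: the trigger is liver function, which is itself a secondary efficacy outcome, and the Background reports an effect of YQSH on ALT.

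Keeping these patients in the efficacy statistics shows an intention to count them, but supplies no observed cirrhosis status. The intention-to-treat principle that the plan invokes calls for outcomes observed after treatment stops, and these rules mean they are not collected.

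**Working it through.** **The plan's own figure.** Sample size gives rates of 5% (control) and 1% (test), two-sided α = 0.05 and β = 0.10:

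n = (1.96 + 1.282)² / [2(asin√0.05 − asin√0.01)²] = 334.5 per arm, stated as 334. Then 334 × 1.2 × 2 = 801.6, stated as 802, or 401 per arm. Both reproduce.

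**What LOCF records.** For a patient removed between baseline and week 52, baseline is the only scheduled cirrhosis observation, so the imputed value is no cirrhosis. If a share d of an arm is removed, with risk r among those removed:

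recorded rate = true rate − d × r

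**Inputs and assumptions.** From the document: 401 per arm, 5% and 1%, a chi-square test at two-sided 0.05, and a 20% attrition allowance (0.20 × 401 ≈ 80 per arm). Assumed: the values of d and r, that all removals fall before week 52, and that every cirrhosis in a removed patient is missed. The last two make each result the extreme for its chosen d and r. Power is exact, for the Pearson chi-square without continuity correction.

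**Equal removal, true rates 1% and 5%** (power with no removal: 94.2%)

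| Removed, each arm | Risk in removed | Recorded, YQSH and placebo | Power |
|---|---|---|---|
| 5% | average | 0.95%, 4.75% | 93.0% |
| 10% | average | 0.90%, 4.50% | 91.6% |
| 20% | average | 0.80%, 4.00% | 87.8% |
| 5% | twice the arm's risk | 0.90%, 4.50% | 91.6% |
| 10% | twice the arm's risk | 0.80%, 4.00% | 87.8% |
| 20% | twice the arm's risk | 0.60%, 3.00% | 75.2% |

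In events: placebo expects 401 × 5% ≈ 20. At 20% removal, 80.2 × 5% ≈ 4 are lost at average risk, and 80.2 × 10% ≈ 8 at twice the risk.

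**Unequal removal, no true effect (5% in both arms).** Chance of a significant result favouring YQSH (2.4% with no removal):

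| Risk in removed | YQSH loses 10%, placebo 5% | YQSH loses 5%, placebo 10% |
|---|---|---|
| 5% | 3.5% (4.50% vs 4.75%) | 1.6% |
| 10% | 5.2% (4.00% vs 4.50%) | 1.0% |
| 15% | 7.7% (3.50% vs 4.25%) | 0.6% |

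(Recorded rates in brackets, YQSH first; they swap in the last column.)

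**Unequal removal, true rates 1% and 5%.** With 5% removed on YQSH and 10% on placebo, power is 90.4% at average risk (0.95% vs 4.50%) and 84.5% at twice the risk (0.90% vs 4.00%).

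**The case against.** - **Wording.** The first sentence closes a paragraph about ceasing treatment, so stopping the trial could mean stopping the drug, and a condensed article may leave retention rules to the full protocol. That reading is possible for the first sentence. It is hard to hold for the second, whose list includes lost contact and self-withdrawal, and the section refers to cessation of treatment where it means the drug. Nor is this a detail that a later analysis plan could settle, because it cannot recover assessments that were never made.
- **Other follow-up.** Close follow-up is promised in the same section, adverse events are tracked to resolution (Harms), and safety tests run to the end of follow-up (Safety outcomes). This makes it less likely that every cirrhosis is missed in the liver-abnormality group. None of it schedules a cirrhosis assessment.
- **Per-protocol set.** Comparing it with the FAS gives some view of the imputation. But it drops the removed patients, so it cannot show what happened to them.
- **Benchmark.** The plan aims at 90% power after attrition. Exact power is 89.8% with 334 per arm and 88.6% with 321 (80% of 401). Against these, 87.8% is a loss of only 1 to 2 points. This is fair: among the equal-removal cases, only 20% at twice the risk is a serious loss. That case spends the whole attrition allowance on high-risk removals, although attrition also covers withdrawals and losses that no rewording recovers.
- **Imbalance.** The trial is double-blind and the documents give no removal rates by arm. The false-benefit figures are therefore illustrations.
- **Use of other drugs.** Read literally, this reason would catch the hepatoprotective drugs that the section permits and the non-antivirals that Concomitant care only asks to be recorded. Read in context, it probably means prohibited or confounding drugs. This is loose wording, and the concern does not depend on it.

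**Conclusion.** The concern holds. Followed as written, the plan records patients removed before week 52 as free of cirrhosis, unless it is found by chance between visits. Patients removed after week 52 keep their week-52 result and are not affected in this way.

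The mechanism is certain from the text; its size and direction are not. Equal removal at average risk costs little power. Removal concentrated in high-risk patients costs more, down to 75.2% in the most severe equal-removal case tabulated. Unequal removal can move the chance of a false significant benefit either way, from 2.4% to anywhere between 0.6% and 7.7% over the ranges assumed. With only about 20 placebo events expected, losing 4 to 8 matters. The change should be made, though nothing in the documents shows that the trial's conclusion is already compromised.

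**What to change.** Reword the two sentences in Modifications so that they end study treatment and not trial participation:

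- *Otherwise, study treatment is stopped permanently; the patient remains in the trial.*
- *If the following conditions occur, subjects should discontinue study treatment and remain in follow-up.* Withdrawal of consent and lost contact would be the only reasons for making no further assessment.

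Everyone else keeps the planned cirrhosis assessments at week 52 and at the follow-up visit, and enters the FAS with the observed result. LOCF is then largely confined to patients who withdraw consent or are lost. Some who miss visits may still lack a result.

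The cost is two sentences, a notice to sites and notification of the ethics committee by the amendment route under Trial status. The examinations and visits are already planned, and the safety stop of the drug is unchanged. Sites must make the effort to retain patients who are off treatment, and patients already taken off the trial would have to be asked to return.

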#### Sample size

The aim of this study is to reduce the annual incidence of cirrhosis from 2% ~ 10% [30] to 1% in patients with CHB. Therefore, according to the sample size estimation formula for comparison of two sample rates, the incidence of target events is less than 0.2 (or 0.3) or greater than 0.8 (or 0.7), shown as follows:
$$ \mathrm{n}=\frac{{\left({u}_{\alpha }+{u}_{\beta}\right)}^2}{2{\left({\mathit{\sin}}^{\hbox{-} 1}\sqrt{p_e}{\hbox{-} \mathit{\sin}}^{\hbox{-} 1}\sqrt{p_c}\right)}^2} $$

Here *p*_*e*_ and *p*_*c*_ represent the incidence rates of the test group (YQSH group) and placebo group (control group), respectively. The positive event rate (*p*_*c*_) in the control group is 5%, while the target event rate (*p*_*e*_) in the test group is set to 1%. Since the values of p_e_ and p_c_ are small, the degree is measured in radians, α = 0.05, and β = 0.10. In this study, a two-sided test was chosen, *u*_0.05_ = 1.96, *u*_0.10_ = 1.282, *p*_*e*_ = 0.05, *p*_*c*_ = 0.01. The calculated sample size of each group is approximately 334 cases. Therefore, allowing for 20% attrition, the total number of patients required for this trial is 334*(1 + 20%)*2 = 802 cases, with 401 in each group.

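### The rule that subjects leave the trial for non-adherence, deterioration or incomplete data keeps no cirrhosis assessment afterwards, so those removed before week 52 are scored cirrhosis-free by default

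*Protocol article*

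**What the plan says.** Modifications (under Interventions) contains two rules.

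- **Liver-function rule.** An abnormality such as ALT above twice the upper limit of normal comes first: "this should prompt temporary or permanent cessation of treatment". The investigator may add hepatoprotective drugs and is to follow the patient closely. If the values normalise, the patient may continue. If not: "otherwise, the patient will stop the trial permanently for safety reasons".
- **General list.** "If the following conditions occur, subjects should discontinue the trial: (1) poor compliance, irregularly taking medicine, failure to revisit or revisit on time". Item (2) is "some combined diseases or complications, or deterioration during the trial". Item (4) is use of other drugs or dosing outside the rules, and item (6) is inability to give complete information. Items (3) and (5) are self-withdrawal and lost contact.

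Four other places decide what this does to the primary outcome.

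- Exclusion criteria: "The exclusion criteria are as follows: (1) patients with cirrhosis".
- Primary outcome: "The primary outcome is evaluated before the treatment, at 52 weeks of treatment, and at the 52 ± 2 weeks follow-up visit".
- Analysis population and missing data: all randomised subjects enter the full analysis set (FAS) under the intention-to-treat principle, and missing data of early withdrawals are filled by LOCF. The per-protocol set (PPS) requires 80–120% compliance and no co-medication that affects the efficacy evaluation.
- Data collection plan and data management: losses due to ineffectiveness go into the efficacy statistics. For patients who responded but "could not complete the entire course, and those lost to follow-up, these data will be included in the efficacy statistics". Adherence repeats this in similar words.

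Additional analyses plans no sensitivity analyses.

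**The concern.** Stopping study drug and leaving the study are different events, and the Modifications section does not keep them apart. The liver rule begins with treatment and ends with the trial. The general list applies one instruction both to patients who can no longer be observed and to patients who could easily be observed. Items (1), (2), (4) and (6) and the unresolved liver abnormality belong to the second kind.

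The reasons are not neutral. Deterioration and an unresolved liver abnormality can be related to progression towards cirrhosis, and non-adherence may be related to prognosis and possibly to treatment. If such patients leave before week 52, their FAS membership survives but their primary outcome is imputed, and it is imputed as a good one. Equal loss of would-be cases in both arms costs power. Unequal loss biases the comparison in either direction. With no sensitivity analysis planned, neither would show in the results.

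Item (4) is also hard to apply uniformly at five centres. Concomitant care has non-antiviral medicines simply recorded, and the liver rule lets the investigator add drugs. Read literally, item (4) removes anyone who combines the trial drug with another.

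**Working it through.** **Step 1. The plan's own figure.** Sample size uses 5% (control) against 1% (YQSH), two-sided α = 0.05, β = 0.10 and the arcsine formula:

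n = (1.96 + 1.282)² / [2(asin√0.05 − asin√0.01)²] = 334.5 per arm, stated as about 334.

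It then continues: "allowing for 20% attrition, the total number of patients required for this trial is" 334 × 1.2 × 2 = 801.6, stated as 802, or 401 per arm. Both figures reproduce. The real allowance is 802 − 2 × 334 = 134 patients, and 134/802 = 16.7%.

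**Step 2. What LOCF assigns.** For a patient who leaves before week 52, the only scheduled cirrhosis observation is the one before treatment. Entry excludes cirrhosis, so that observation is negative, and LOCF carries the negative forward. The exception is a cirrhosis diagnosis at an unscheduled examination. A patient who leaves after week 52 carries the week-52 status, so only later cases are missed.

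**Step 3. Power if removed cases become non-events.** Method: uncorrected two-sided χ² test at 0.05, exact binomial enumeration. Design reference: 5% against 1% with 334 evaluable per arm gives 89.8%; 401 per arm with no loss gives 94.2%. If a fraction f of would-be cases is removed in both arms, the observed rates are 5%(1 − f) and 1%(1 − f) with 401 per arm.

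| f (assumed) | Rates | Power |
|---|---|---|
| 0.167 (exits unrelated to prognosis, at the allowance) | 4.17% v 0.83% | 89.2% |
| 0.20 (f = 0.40, half found at an exit examination) | 4.0% v 0.8% | 87.8% |
| 0.30 | 3.5% v 0.7% | 82.4% |
| 0.40 | 3.0% v 0.6% | 75.2% |

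If 16.7% leave, the risk of leavers relative to stayers is (f/0.167)/((1 − f)/0.833). That is 2.1 for f = 0.30 and 3.3 for f = 0.40.

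**Step 4. Type I error if removal differs by arm.** No true effect, 401 per arm, 20% of cases removed in one arm and 40% in the other (assumed):

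- True rate 5%: observed 4.0% v 3.0%, type I error 11.7%. If half of the removed cases are found at exit (net 10% v 20%), it is 6.2%.
- True rate 2%: observed 1.6% v 1.2%, type I error 6.5%. With half found at exit it is 4.9%.

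**Step 5. Dilution if patients off drug are followed.** Suppose 16.7% of YQSH patients stop drug (assumed) and all 401 per arm are assessed.

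- They lose half the benefit: YQSH rate 1% + 0.167 × 0.5 × 4% = 1.33%, difference 3.67 points, power 87.1%.
- They lose all of it: 1% + 0.167 × 4% = 1.67%, difference 3.33 points, power 77.0%.

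**The case against.** **The wording may mean less than it says.** The list stands under Interventions, in a section that opens with stopping treatment, and the word trial may loosely mean trial treatment. The article condenses a fuller protocol that may provide for off-drug visits. This stands as a reason for moderate confidence. A reader might infer that the plan forbids assessing these patients or drops them from the analysis. The documents do not support that: the FAS holds everyone randomised, and no sentence bars a later examination. But the article does state a removal rule and an imputation rule, and together they give the default result in step 2.

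**Some follow-up is promised.** The liver rule asks for close follow-up, adverse events are tracked until they resolve or follow-up is judged unnecessary, and safety indicators are monitored to the end of follow-up. Losses due to ineffectiveness enter the efficacy statistics. This makes an unscheduled diagnosis less remote. None of it schedules a cirrhosis assessment after discontinuation or sets a failure rule. Including the data covers only what was already collected.

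**The size is assumed.** This stands. The trial is double-blind with a matched placebo, and nothing in the article supports a twofold difference in removal between arms. Late visits and incomplete information are not shown to be related to prognosis.

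**The scoring harm comes from LOCF.** This stands too. LOCF treats true dropouts the same way, and a change to the removal rule does not reach them. If LOCF is also criticised separately, these figures must not be counted twice.

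**Conclusion.** The point holds as a badly fixed rule that should be corrected, with moderate confidence because the wording is ambiguous. As written, observable patients may leave the study for reasons that can be related to prognosis, no cirrhosis assessment is kept for them, and LOCF scores those removed before week 52 as cirrhosis-free unless an unscheduled examination shows otherwise.

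Size and direction are unknown. At the planned allowance, with exits unrelated to prognosis, the cost is 0.6 points of power (89.8% to 89.2%). A material loss needs prognosis-related removal: 82.4% or 75.2% power if 30% or 40% of would-be cases in both arms are lost. An inflated type I error needs removal that differs by arm, and it returns close to nominal if half of the removed cases are found at exit. All these fractions are assumptions. A reader might infer that the trial will be biased, or biased in favour of YQSH. The documents support neither; they show only that the rule leaves the primary comparison open to bias in either direction.

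**What to change.** In Modifications:

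1. Drop items (1), (4) and (6) as compulsory reasons to leave the trial or to stop drug. Merely rewording them as stopping study drug would still take patients off treatment for a late visit, irregular dosing or an incomplete record, and would add avoidable dilution.
2. For item (2) and the unresolved liver abnormality, say that study drug may be stopped on clinical grounds.
3. State that only withdrawal of consent or lost contact ends outcome collection.
4. State that all other patients, on or off drug, keep the scheduled week-52 and end-of-follow-up cirrhosis assessments and are analysed as randomised in the FAS. Compliance and co-medication are handled through the PPS, which already has criteria for both.

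The cost is protocol wording and already scheduled visits for patients off drug. Following them may dilute the effect: power is about 87% if 16.7% of YQSH patients stop drug and lose half the benefit, and 77% if they lose all of it. The change buys a comparison protected from selective loss of outcomes; it does not promise more power.
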